## 4.17 Data collection and management

The principal investigator will train the data collectors and supervisors for two
consecutive days on instruction; in the quantitative method, study guides, role-plays
(demonstration), informed consent, how to approach participants, how to collect data using
mobile health, ethical procedure and general information and the objective of
the study. The data will be collected by using a mobile-based application called open data kit
(ODK). In the initial step, a pre-intervention survey will be conducted after the randomization and allocation. And there will be two times data collection including the pre-intervention and post-intervention data. The data will be collected by 4 months interval to have a good longitudinal data. The type of data will be panel data with repeated cross-sectional. Experienced data collectors with health background and Hadiyisa speaking will be recruited to collect the data. Besides, a master holder with health profession will be employed to supervise the whole data collection process.

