## Randomization

There are a total of 12 clusters for this cluster randomized trial. The researcher and kebele leaders, religious leaders and HEWs will conduct the randomization to produce comparable groups and eliminate the source of selection bias in the assignment of kebeles to the intervention and control groups. Simple randomization with a 1:1 allocation will be applied to assign clusters to either control or intervention groups. First, 12 nonadjacent clusters will be selected by a lottery method. Then, the 12 clusters were listed alphabetically. A list of random numbers will be generated in MS Excel 2010 and the generated values will be fixed by copying them as “values” next to the alphabetic list of the clusters. These are arranged in ascending order according to the generated random number. Finally, the first 6 clusters will be selected as intervention clusters and the last 6 as control clusters. A statistician that will be blinded to study groups and not participated in the trial will do the generation of the allocation sequence and the randomization of clusters (Figure below). The intervention group is assigned to receive training from religious leaders on maternal and neonatal health and the control group will be left to continue the current practices.

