The first training session will be conducted at the beginning of the intervention whereas the second session of similar content will be repeated after one month of the first intervention session and the third and fourth training sessions will be after one months of the second intervention session. After training sessions, every participant will receive a copy of the visual materials (posters) containing the key messages for promoting prenatal health behaviours. Direct, interactive and participatory learner and activity oriented instructional strategies will be delivered. Talks, group discussions, group work exercises, demonstrations, role plays, storytelling, simulation, case studies and problem-solving will be used to enhance knowledge, attitude, and behaviours on maternal and neonatal health (Table 2 shows over protocol of intervention).

Overall project coordination: by PI and co-PIs

Step 1:

Formative assessment: perception of mothers’ on engagement of religious leaders in promoting maternal health, and role of religious leaders in promoting maternal and child health: a qualitative exploration of religious leaders’ perspective

Baseline study: Intervention protocol development, data collection and analysis

Developing strategies and SBCC material flip chart, information card and poster and recruiting religious leaders

Randomization of the clusters in to intervention and control groups

Step 3: Pregnant mothers’ training by trained religious leaders

Training contents: Maternal health message contents, flip chart, poster, group education and group discussion

**Session 1:** Major causes of maternal and new-born Illness and death

**Session 2:** Focused Antenatal Care and danger signs during pregnancy

**Session 3:** BPCR and danger signs during labor and childbirth

**Session 4:** Components of PNC and Postnatal danger signs and neonatal danger signs

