## 4.14 Cluster and individual selection

Health posts are eligible for trial. All 40 health post units in the selected districts are eligible and 12 health posts are randomly selected for the trial using a computer random number generator. Pregnant mothers less than or equal to 20 gestational age are eligible to participate in the trial if they are living in the villages within the selected health post village areas. Baseline surveys will be commenced in May 2022 and end line surveys are scheduled to begin after four months of intervention.

The pregnancy surveillance for this study will be conducted among currently married women of reproductive age (15–49 years) permanently living in the selected districts. A pregnancy test will be done for the study women at the beginning of the surveillance. Identifying pregnant women will be a two-step process. First, all women will be screened using pregnancy screening questions adapted from the Kenya family planning enrolment questionnaire as published in the Lancet (Stanback J et al, 199) (Table 2). If the answer to at least one of the six pregnancy screening questions is ‘yes’, pregnancy will be ruled out. Women who respond in a way that suggested the possibility of being pregnant is asked to provide a urine sample for a pregnancy test, which will be done using a dipstick in the respondent’s home. Once pregnancy is detected, the women will be recruited for the trial study.

Table 2 Pregnancy screening questions adapted from Kenya family planning screening questions

| S/No | Items | Yes or No |
| --- | --- | --- |
| 1 | Have you given birth in the past 4 weeks? |  |
| 2 | Are you less than 6 months post-partum or fully breastfeeding and free from menstrual bleeding since you had your child? |  |
| 3 | Did your last menstrual period start with in the past 7 days? |  |
| 4 | 4 Have you had a miscarriage or an abortion in the past 7 days? |  |
| 5 | Have you abstained from sexual intercourse since your last menses? |  |
| 6 | Have you been using a reliable contraceptive (pills, injectable, and Norplant) method consistently and correctly? |  |

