## 4.15 Intervention assignment and masking

Randomisation is stratified by kebeles, with 12 clusters in the district allocated to either control or intervention in a public randomisation meeting. From each clusters (kebele), local stakeholders (HEWs, kebele leaders and religious organization leaders) are invited, a number is allocated to each cluster, the numbers are written on small plastic balls, and placed the balls in a dark bag. Each participant is asked to draw one ball from the bag and read out the cluster numbers out until all balls are picked. The cluster numbers are written on a sheet of paper in order of selection. Participants then place 12 pieces of paper numbered 1 to 12—each corresponding to a unique allocation sequence generated by an independent statistician—in the dark bag, and asked a participant to select a paper and read out the number. The corresponding sequence is then used to publicly allocate each cluster to one of two groups. Because of the nature of the intervention being tested, the intervention team could not be masked to allocation. The data collection team will be masked to allocation, both at the cluster and at the individual level. Blinding is done to control for bias as follows. The researcher does not inform the study interventions and hypothesis for the participants who participate during the randomization of the kebeles into study groups.

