**Participant timeline**

Clusters will be enrolled and randomized to trial arms in June 1, 2022. Baseline recruitment and interviewing of women within study clusters began in June 5, 2022 and will be completed after four months of intervention.

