**Intervention fidelity**

Fidelity of the intervention will be maintained based on the National Institutes of Health Behavioural Change Consortium developed best practice recommendations (Bellg et al., 2004). The intervention design has conceptual framework. Non adjacent clusters will be selected to prevent information contamination. Equal numbers of clusters will be taken for the intervention and control groups from each district to balance variations. The intervention process will be pretested before the implementation of the trial. Each pregnant mother will receive equal numbers and frequencies of training, and the lengths of contacts within an intervention group will be similar to make the process standardized. Group education training will be given in a group using a training manual, role-playing, and mock counselling practice. The competency of recruited religious leaders will be monitored by pre-post training test. The test focuses on knowledge and attitudes towards intervention key messages. If the post-training test score of the trained religious leaders is below acceptable range, retraining will be given on identified gaps of intervention messages. Training sessions will be randomly selected for process evaluation and all selected sessions will be evaluated by one process evaluator. The process observer rated the educator using a ‘yes/no’ rating system on items such as using a training guide, provision of the whole content, duration and frequency of training, preparedness, accuracy, and ability to properly respond to questions. Intervention receipt will be assessed using checklists on knowledge of the pregnant mothers on maternal health behaviour through interviewing about their understanding of the core contents of the intervention. Intervention enactment will be assessed on utilizations of antenatal care and skilled delivery.

Routes of **persuasive message**

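### The protocol contradicts itself on whether women are recruited before or after kebeles are publicly allocated, and neither of its two allocation methods delivers the district balance it promises

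*Protocol*

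**What the plan says.** **Order of steps.** Section 4.17 states that "a pre-intervention survey will be conducted after the randomization and allocation". The participant timeline gives dates in the same order: "Clusters will be enrolled and randomized to trial arms in June 1, 2022", and then "Baseline recruitment and interviewing of women within study clusters began in June 5, 2022". The flow diagram in section 4.11 also places randomisation above recruitment. Section 4.14 says otherwise: "Baseline surveys will be commenced in May 2022". Figure 3 (section 4.13) lists "Baseline study: Intervention protocol development, data collection and analysis" ahead of the randomisation of clusters within its first step.

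**Method of allocation.** The Randomization section states: "Simple randomization with a 1:1 allocation will be applied to assign clusters to either control or intervention groups". Random numbers are generated in Excel against one alphabetical list, which is then sorted; the top six clusters become intervention and the bottom six control. That section first says that the researcher and local leaders carry out the randomisation, and later that an uninvolved statistician does. Section 4.15 describes something else: "Randomisation is stratified by kebeles, with 12 clusters in the district allocated to either control or intervention in a public randomisation meeting". There, numbered balls are drawn to order the clusters, and one of 12 prepared sequences is drawn and applied in public. Health extension workers and administrative and religious leaders from each kebele are invited.

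**District.** Under Intervention fidelity the protocol promises: "Equal numbers of clusters will be taken for the intervention and control groups from each district to balance variations".

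**Safeguards.** Section 4.15 masks the data collectors and withholds the interventions and hypothesis from those attending the meeting. Section 4.14 screens all women with six questions, followed by a urine test where pregnancy is possible.

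**The concern.** Randomising kebeles makes the kebeles comparable on average. It does not by itself make the enrolled women comparable if they enter after the allocation of their kebele is known. Enrolment depends on the woman's willingness (section 4.5) and on consent given after she is identified (section 4.21). It also depends on her own answers to the screening questions. If any of these shifts with public knowledge of the arm, the two groups differ at entry, and no later step restores the comparison.

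The method of allocation is a separate matter. With two descriptions that cannot both be followed, a reader cannot tell which was used. The stratification named in 4.15 is empty because the kebele is itself the cluster. The factor that the protocol does want balanced, district, appears in neither mechanism. With only 12 clusters, chance imbalance on district is common and adds noise to the arm contrast.

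**Working it through.** The plan states no figure for either risk, so there is none to reproduce. The inputs are 12 clusters allocated 6:6 (Randomization section), two districts (section 4.9), and the design rates of 26% and 41% for skilled delivery (section 4.8).

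**1. Order, side by side.**
- Allocation first: 4.17 in words; the participant timeline by date (1 June, then 5 June 2022, four days later); the 4.11 diagram by position.
- Baseline first: 4.14 by date (May 2022, before 1 June); Figure 3 by position.

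The boxes of both figures were read here as text, so position is weaker evidence than the statements in 4.17, 4.14 and the timeline. Those three alone already conflict.

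**2. What is open to influence if allocation comes first.** The public meeting would precede surveillance, screening, consent and the baseline interview. Screening excludes a woman on one yes among six self-reported answers, and consent is her own decision. Both would take place in a kebele whose arm has been announced.

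**3. Whether the analysis could repair it.** Section 4.19 plans adjustment for baseline differences through a period-by-allocation interaction. A woman enrolled before 20 weeks has no baseline value for skilled delivery in this pregnancy. The questionnaire asks only where her last child was delivered (item 324), and a woman in her first pregnancy has no answer to that.

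**4. Probability of district balance.** If one district supplies *a* of the 12 kebeles, the chance that *k* of them fall in the intervention arm is C(a,k) × C(12−a, 6−k) / C(12,6), with C(12,6) = 924. This holds for the Excel sort. It holds equally for the ball draw with any 6:6 sequence, because the draw puts all 12 clusters in random order. The protocol does not give the number of kebeles per district, so *a* is assumed.
- *a* = 6: exact 3:3 balance = 20 × 20 / 924 = 400/924 = 43.3%. A 4:2 split in either direction = 2 × 225/924 = 48.7%. A 5:1 split or worse = 2 × (36 + 1)/924 = 8.0%.
- *a* = 8 (near the population share, 148,339/229,196 × 12 = 7.8): exact balance = 70 × 6 / 924 = 420/924 = 45.5%.
- *a* odd: exact balance is impossible.
- Randomising separately within districts that each hold an even number of kebeles: balance is certain.

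**5. What an imbalance could do (illustration, 6 + 6 kebeles of equal size).** With a between-district difference of *d* points in skilled delivery, a 4:2 split moves the arm contrast by *d* × (4−2)/6 and a 5:1 split by *d* × (5−1)/6. For assumed *d* of 5 to 20 points this is 1.7 to 6.7 and 3.3 to 13.3 points, against a target effect of 15. The protocol gives no value of *d*.

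**6. What differential enrolment could do (illustration).** Suppose a share *s* of intervention recruits would have a 60% rather than 26% chance of skilled delivery, with no counterpart in control kebeles. The shift is *s* × (0.60 − 0.26): 1.7 points at 5%, 3.4 at 10% and 6.8 at 20%. Both the share and the 60% are assumptions.

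**The case against.** A reader might infer that the health extension workers and leaders who attend the allocation meeting also find and enrol the women. The documents do not say so. Section 4.13 has such local figures helping to arrange the training venue and to recruit religious leaders. Women are found by surveillance, tested at home and interviewed by clinical nurses. The data collectors are to be masked, those at the meeting are not told the interventions or hypothesis, every woman is screened, and an absent woman is replaced by random selection. All of this stands and lowers the risk. It does not close the gap: the women's own answers and consent are not masked, and keeping collectors unaware of an allocation announced in the kebeles where they work is difficult.

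A reader might also infer that the protocol disregards district. It does not, since the fidelity section promises balance; the fault is that no written step delivers it. Nor is chance imbalance under valid randomisation a systematic bias. It adds variance, and with 6 + 6 kebeles most of it is the milder 4:2 kind.

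The Excel sort and the ball draw are both random, and both rely on a statistician outside the trial. Their conflict is one of documentation and does not itself create recruitment bias.

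Finally, locking a participant list protects the endline comparison only if those women are followed. The protocol describes repeat cross-sectional surveys in 4.11 and panel data in 4.17, so that must be settled too.

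**Conclusion.** The point holds as two contradictions. First, the protocol gives both orders for recruitment and allocation, and the allocation-first order leaves room for differential enrolment in kebeles whose arm is public. The documents support that as a possibility only: they do not show that it would occur, and the 1.7 to 6.8 points above illustrate scale and are not an estimate. Second, the two allocation procedures are incompatible, one names a stratum that has no meaning, and neither secures the promised district balance. That balance would arise by chance in 43.3% (6 + 6) or 45.5% (8 + 4) of allocations, with the splits assumed. The consequence for the effect estimate depends on a between-district difference that the protocol does not give. Both matters need settling before allocation is disclosed, because neither the order nor the mechanism can be changed afterwards.

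**What to change.** - **Order.** Adopt the sequence already in 4.14 and Figure 3. Complete surveillance, consent and baseline interviews in all 12 kebeles, lock the participant list, and only then disclose allocation. Correct 4.17, the participant timeline and the 4.11 diagram to match.
- **Follow-up.** State that the listed women are followed to endline, and reconcile the panel and repeat cross-sectional descriptions in 4.11 and 4.17.
- **Allocation.** Describe one procedure: a sequence from an independent statistician, randomised separately within each district, with an even number of kebeles per district. It may still be revealed at the public meeting. State the number of kebeles per district. Remove the stratification by kebele, the reference to simple randomisation, the second mechanism, and the conflicting statement of who randomises.
- **Analysis.** Include district as a covariate in the outcome models.

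The cost is rewording, reordered fieldwork and a short delay to allocation (the protocol allows 15 days for baseline data collection). District uses one degree of freedom, which is noticeable but affordable with 12 clusters.

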**Baseline Data Collection**

Six clinical nurses for data collection and two supervisors with master holder in public health will be used. Intensive training will be given for data collectors and supervisors on the item. The data collectors and the supervisors will be assigned to a different cluster of a given district. Interviews are expected to last approximately 1 h and will be conducted in a quiet, private space at the homes of the women. If selected women are absent from their homes, interviewers will visit households up to three different days/times to attempt to interview them before the woman will be replaced with another randomly selected woman. The data will be collected for a total of 15 days.

**End line Data collection**

The same procedure with the baseline data will be repeated to collect the end line data after one month of delivery. Six data collectors with health background will be used to collect the data. Two supervisors will be assigned to check for the daily activity, consistency, and completeness of the questionnaire and to give appropriate support during the data collection process. The data collectors and the supervisors will be assigned to a different cluster of a given district.

Qualitative Data collection

Focus group discussions and in-depth interviews among religious leaders and pregnant mothers will be conducted. Trained graduate research assistants will conduct Focus group discussions and in-depth interviews. Data will be collected by recording interviews by audiotape. Brief field notes will be taken during interviews. Field notes will be carefully taken during data collection and analysis. These notes will collect observations and assumptions about what will be heard or observed and personal narratives about what will be felt by the researcher during an interview.

## 4.18 Data Quality Control

To assure the quality of the data, data collectors and supervisors will be trained and a regular supervision and follow-up will be made by supervisors and the principal investigator. In addition, a regular check-up for completeness and consistency of the data will be made on daily basis. The questionnaire is translated into Amharic language and back-translated into English by translators who are blind to the original questionnaire. To make the questionnaire standard, reliability and validity test will be done for scale variables. Pilot test and Pre-test of the tool will be carried out in the area which has similar characteristics with the study population in Anlemo district will be done before two weeks of the actual data collection to ensure clarity, wordings, logical sequence and skip patterns of the questions. The pre-tested sample will be not included in the study and modification will be made.

For the qualitative study: Silent and comfortable places and convenient times will be selected and arranged to conduct, in-depth interview with religious leaders so as to allow maximum concentration. Study participants will also be made to give a true answer through explaining the purpose and importance of the study and assuring the confidentiality of data they are going to provide. To enhance inter-coder reliability, the coders each will independently apply the code book to a selected and rich transcript and review any differences in their coding, which will be discussed and resolved.

**Operational definition**

**Skilled delivery service utilization**

Skilled delivery service utilization will be measured based on women who gave birth in health center and hospital by assistance of health professionals that have midwifery skills including Midwife nurse, Nurse, Health Officers and Doctors *as* reported by the participant.

**Antenatal care service utilization**

Antenatal care service utilization will be measured based on “at least one ANC attendance” (Women who have attended at least one ANC check-up during their current pregnancy) and “four or more ANC attendance” (Women who attended four or more ANC visits) during their current pregnancy as reported by the participant.

